### Limitations and bias

The allocation is non-randomised with selection based on intervention criteria determined by the implementer so the risk of residual confounding cannot be excluded. The choice of the control group is also dependent on the implementer’s information about the non-intervention in the area in the short term (5-year period). To limit the potential for bias arising from our non-randomised design, we will select control group with as similar as possible socioeconomic and environmental characteristics to those of their matched intervention clusters.

We will perform the impact calculation through the double differentiation of the averages of the results found between the intervention and control clusters before and after the sewerage intervention. The mitigation of bias will be carried out through the control of fixed effects of time and location between different intervention and control clusters over the years of evaluation.

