**Methods and analysis:**

This matched quasi-experimental study design using non-randomised intervention and control clusters was designed to assess the effectiveness of an urban simplified sewerage intervention in the low-income communities of Salvador, Brazil. The intervention consists of household-level piped sewerage connections and community engagement and public involvement activities. A cohort of 1400 adult participants will be recruited and grouped into eight clusters consisting of four matched intervention-control pairs with approximately 175 individuals in each cluster in baseline. The primary outcome is the seroincidence of *Leptospira* infection assessed through five serological measurements: one preintervention (baseline) and four postintervention. As a secondary outcome, we will assess *Leptospira* load in soil, before and after the intervention. We will also assess *Leptospira* exposures before and after the intervention, through transmission modelling, accounting for residents' movement, contact with flooding, contaminated soil and water, and rat infestation, to examine whether and how routes of exposure for *Leptospira* change following the introduction of sanitation.

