## Methods and analysis

### Overview of study design

This is an intervention trial with a cluster non-randomised controlled trial, with eight clusters (four intervention and four control), including longitudinal serological follow-up of 1400 adults’ residents from disadvantaged urban communities at high risk for leptospirosis transmission in Salvador, Bahia, Brazil. The primary outcome will be *Leptospira* infection. Each pair of intervention and control clusters will be allocated in distinct hydrological sub-basins with distances from 1000 to 1500 m apart. Clusters will be matched on socioeconomic status (SES), topographic or hydrological characteristics, population density, and *Leptospira* seroprevalence. The cluster selection will also consider exposure to the pathogen by selecting houses that are located to similar distances to new sewerage system and control open sewers. The intervention aims at a combination of sanitation (simplified sewerage intervention) and community engagement activities.

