### Outcomes

#### Primary outcome measure

The study trial will consist of three specific phases: (1) baseline; (2) sanitation intervention implementation; (3) follow-up of the residents and evaluation of the sanitation intervention (figure 2). During the phase (1) a baseline survey will be conducted to characterise the demographics, SES and *Leptospira* seroprevalence in each cluster. During the phase (3) biannual serosurveys in the cohorts will be conducted to measure the primary outcome, *Leptospira* asymptomatic infection, and estimate the risk of infection during the dry and rainy seasons. The field team will collect blood samples from eligible participants with age ≥18 years. A blood sample (10 mL) will be collected from each study participant and examined for *Leptospira* antigen using the microscopic agglutination test diagnostic (MAT).^4^ MAT is the standard test to determine *Leptospira* infection in longitudinal studies and *Leptospira* infection will be defined as a fourfold rise in MAT titre or seroconversion (negative to ≥1:50) between samples from consecutive serosurveys. We will use a panel of six reference strains: representing *L. interrogans* serovars Autumnalis strain Akiyami A, Canicola strain H. Utrecht IV and Icterohaemorrhagiae strain RGA, *L. borgpetersenii* serovar Ballum strain MUS 127, *L. kirschneri* serovar Cynopteri strain 3522C and Grippothyphosa strain Duysterand the two clinical isolates: *L. interrogans* serovar Copenhageni strain Fiocruz L1-130 (isolated locally in 1996) and *L. santarosai* serogroup Shermani strain LV3954 (isolated locally). This procedure had the same performance in identifying MAT seroconversion in our prospective studies^4 14^ compared with the WHO recommended panel of 19 reference serovars. The screening will be performed with serum dilutions of 1:50–1:100. When agglutination is observed at 1:100, the sample will be titrated to determine the highest titre. As part of quality control procedures, two independent evaluations will be conducted for 8% of the samples and all samples from infected subjects.

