### Statistical analysis

Descriptive statistics will be employed to report the demographic, social, economic or environmental characteristics between the study clusters (intervention and control clusters). For the primary outcome, we will apply quasi-Poisson regression to estimate the incidence rate ratio of *Leptospira* infection. We will also evaluate the effect of the intervention on *Leptospira* infection risk using mixed-effects logistic regression models to account for clustering of the observations within study units and across repeated measures for individuals. We will model the overall effect of the intervention on infection risk while controlling for baseline sewerage and flooding exposure and potential confounding variables, such as age, sex, indicators of the socioeconomic level, and rainfall intensity during an annual period, which are presumably unrelated to the intervention (figure 1).

For the secondary outcome, we will conduct environmental analyses of *Leptospira* load between intervention and control clusters to compare environmental risk. To do this, we will model two leptospiral load outcomes, prevalence (binomial) and concentration (log-transformed), using generalised linear models with random effects to account for clustering within study units. The association between environmental contamination and hypothesised predictors of risk (rat abundance, human movement and ecological data) will also be explored in the model (figure 1).

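### Double differencing with location fixed effects is stated for all outcomes, but the primary outcome, seroincidence, has no pre-intervention value

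*Protocol article*

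**What the plan says.** - **Bias control (Limitations and bias).** The section acknowledges non-random allocation and possible residual confounding, then states: "We will perform the impact calculation through the double differentiation of the averages of the results found between the intervention and control clusters", comparing the periods before and after the sewerage works. It adds that bias will be mitigated through "control of fixed effects of time and location between different intervention and control clusters". No outcome is named and none is excepted.
- **Primary outcome and schedule (Abstract, Methods and analysis).** The primary outcome is "seroincidence of *Leptospira* infection assessed through five serological measurements: one preintervention (baseline) and four postintervention". Study population and sample size likewise describes one baseline and three years of follow-up after the intervention.
- **Event definition (Primary outcome measure).** Infection is "defined as a fourfold rise in MAT titre or seroconversion (negative to ≥1:50) between samples from consecutive serosurveys". The baseline survey is described as yielding cluster seroprevalence; the primary outcome is assigned to the follow-up phase.
- **Models (Statistical analysis).** For the primary outcome, a quasi-Poisson regression gives the incidence rate ratio. Mixed-effects logistic models handle clustering and repeated measures, with adjustment for baseline exposure and for confounders given as examples. No before/after contrast appears there.

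**The concern.** Double differencing needs the outcome in both arms in both periods. One blood sample per person gives prevalence; incidence, as defined here, needs two. With a single pre-intervention survey the first of the two differences does not exist for seroincidence.

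This matters because the implementer decides which areas receive sewerage, and there are only four clusters per arm. Double differencing and fixed effects are what the article offers, at the analysis stage, against stable differences between the areas. A reader would take the primary result to be protected in that way. If it is not, any pre-existing difference in incidence that matching and covariates leave behind passes directly into the rate ratio.

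**Working it through.** No stated sample size, power or other figure is in dispute. The check concerns what the design can identify.

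**Step 1: count the incidence intervals.** Inputs: "five serological measurements: one preintervention (baseline) and four postintervention", and infection defined "between samples from consecutive serosurveys".

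- Intervals = surveys − 1 = 5 − 1 = 4: baseline to first post-intervention survey, then three between post-intervention surveys.
- Intervals with both ends before the intervention = pre-intervention surveys − 1 = 1 − 1 = 0.

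The estimator is (post − pre, intervention) − (post − pre, control). Both pre terms are missing.

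**Step 2: can fixed effects identify the effect?** Inputs: eight clusters in four matched pairs, each cluster in one arm throughout, and the interval as the time unit. Each row compares the rank of the design matrix without and with the intervention term.

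| Layout | Columns with intervention term | Rank without | Rank with | Effect estimable? |
|---|---|---|---|---|
| Cluster and time effects, 0 pre and 4 post intervals | 8 + 3 + 1 = 12 | 11 | 11 | No |
| Pair and time effects, 0 pre and 4 post intervals | 4 + 3 + 1 = 8 | 7 | 8 | Yes, post-intervention only |
| Cluster and time effects, first interval relabelled as pre (1 pre, 3 post) | 8 + 3 + 1 = 12 | 11 | 12 | Yes, but that interval spans the works |
| Cluster and time effects, 1 true pre and 4 post intervals | 8 + 4 + 1 = 13 | 12 | 13 | Yes, but needs two pre-intervention surveys |

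In the first row the four intervention-cluster indicators sum to the intervention indicator. Software would drop a column, and the reported coefficient would depend on which one.

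**Step 3: what is at stake in a post-intervention comparison.** Apparent rate ratio = true rate ratio × pre-existing ratio (intervention/control). The article gives no pre-existing ratio, so the values here are assumptions.

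- Control clusters 20% higher, no effect: 1 × 1/1.2 = 0.83.
- True 50% reduction, one of the article's planning effects: 0.50 × 0.8 = 0.40; 0.50 × 1.25 = 0.625; 0.50 × 1.5 = 0.75.

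**The case against.** The strongest reply is that Limitations and bias never says its calculation is the primary estimator. The primary models are under Statistical analysis, need no pre-period, and can be run. Double differencing suits the outcomes measured before and after: soil load, rat activity, movement, well-being and child development. Location could also mean the matched pair, in which case the matrix has full rank. And the section already concedes residual confounding.

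Much of this stands. A reader might infer that the primary analysis cannot be run at all; that is not so. But the sentence on impact is unrestricted, and the paragraph presents it as part of the answer to non-random allocation. If it was meant for other outcomes only, the primary outcome lacks that protection and the text should say so. Pair effects make the model estimable without supplying a before period. Double differencing seroprevalence is possible, but it targets a different quantity. An unseen analysis plan could clarify the scope, but it could not create a pre-intervention interval under this schedule.

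Four other inferences are tempting and not supported:

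- **Baseline serology is unused.** It is used: the baseline sample opens the first interval and decides whether seroconversion or a fourfold rise applies. Nor is adjustment for it excluded, because the listed confounders are examples.
- **Matching on seroprevalence was impossible.** Overview of study design says "Clusters will be matched on socioeconomic status (SES), topographic or hydrological characteristics, population density, and" seroprevalence. Control selection does not repeat it, but that list is not exhaustive, and the article does not say that no earlier serology was available.
- **The soil-load model lacks a before/after term.** Statistical analysis says only "we will conduct environmental analyses of" load between arms, but the Abstract has soil assessed before and after, and Limitations and bias supplies the contrast.
- **The harm can be sized from the between-cluster variation in the sample size section.** That would need an assumed or converted coefficient of variation. Chance imbalance of that kind also affects a randomised eight-cluster trial, so it does not measure the harm from this wording.

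**Conclusion.** The point holds for the primary outcome only. As scheduled, seroincidence has no wholly pre-intervention value, so the before/after double difference is undefined for it. The statement that cluster fixed effects are collinear with the intervention rests on two conditions: location means cluster, and all four intervals count as post-intervention. The absence of a before period rests only on the survey schedule and the event definition.

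The models under Statistical analysis do yield an estimate. It is an adjusted post-intervention comparison, and its freedom from confounding depends on matching and covariates. The possible distortion cannot be sized from the article. Under the assumed pre-existing ratios of 0.8 to 1.5, a true rate ratio of 0.50 would appear as 0.40 to 0.75.

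**What to change.** 1. In Limitations and bias, restrict double differencing and cluster fixed effects to outcomes measured before and after: soil load, rat activity, movement, well-being and child development.
2. For seroincidence, replace cluster fixed effects with matched-pair effects.
3. Adjust for each participant's baseline MAT status or titre, and for cluster baseline seroprevalence where feasible. The latter is constrained: eight clusters less four pair effects and one intervention effect leave 8 − 4 − 1 = 3 degrees of freedom between clusters.
4. State that the primary estimate is a covariate-adjusted, within-pair, post-intervention comparison that does not remove pre-existing incidence differences within pairs.

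The cost is wording and model specification; the baseline MAT result is already collected. The limitation becomes more explicit, and these changes do not restore the before/after control. Within the incidence definition used, only a second pre-intervention serosurvey would do that cleanly, which is a change of design with its own fieldwork. Relabelling the first interval as the before period is a weaker option, because it ends at a survey the article classes as post-intervention and so spans the works.

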### Study population and sample size

To evaluate the effectiveness of the simplified sewerage intervention in reducing the risk of *Leptospira* infection, we plan to recruit an estimated 1400 participants aged ≥18 years, residing in the selected clusters (approximately 175 adults per cluster in baseline). To evaluate the intervention effect on secondary (sewerage contact, environmental pathogen load, long-term child development) and exploratory (arbovirus infections, diarrhoeal disease and enteric infection) outcomes, we plan to increase our sample size by 420 (30%) participants, aged between 6 months and 17 years, totalling 1840 people. We considered a potential loss to follow-up rate of 15%–20% per year. Therefore, by including additional participants, we ensure the maintenance of an appropriate sample size for the outcomes that will be studied. All participants from both intervention and control clusters will be followed over a period of 3 years after the sewerage intervention and a baseline prior to the intervention (figure 2). In the flow diagram, we provide a timeline and trial study phases in detail (figure 3).

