**Figure 3 F3:**
[figure not shown]
Overview of the study procedures, the timeline for study and data collection. Note 1: Each cluster of the study will be formed by a cluster with intervention versus control. The period of activities for each serological survey will take place at the time described in the figure (allocation, recruitment and baseline). Note 2: Update years 1 to 5 will be realised after receipt of the water and sanitation company schedule.

The sample size was estimated using data on *Leptospira* infection from a previous leptospirosis cohort study in Salvador, Brazil.^13^ We divided the previous leptospirosis cohort study^13^ into areas of similar size to that the clusters used trial and calculated the between-cluster variation. Of 1840 individuals participating in the previous cohort, 142 (7.9%) experienced leptospiral infection (k/Intracluster Correlation Coefficient (ICC)=0.03). Power calculations are based on a cluster-level using effect sizes (% decrease in incidence between intervention and control clusters) 40%, 50% and 60%, assuming an infection rate of 0.08 per person-year. All sample size calculations used methods for matched cluster-randomised trials with the study structure of four matched pairs of clusters. Sample size estimates assumed a 12% annual drop-out rate across the 3-year study period.

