#### Other outcomes

##### Human health and well-being

The data will be collected preintervention and postintervention to evaluate the impact on well-being between arms. Other outcomes related to individual and household health and well-being include subjective measures—self-reported general, physical and emotional well-being using the Short-Form Health Survey-12 (SF-12);^32^ perceived living conditions questions; the short version (five items) of the Brazilian Food Insecurity Scale^33^ which measures the perception and experience of hunger over the past 3 months; and objectives measures—productivity through employment and income. We will also evaluate whether there will be a decrease in material and economic loss measures due to floods and landslides—which often occur in the areas without adequate sanitation.

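### For cohort outcomes with a baseline value, double-differencing cluster averages is biased if outcome-related loss differs between arms; a person-level model would use data already collected

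*Protocol article*

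**What the plan says.** Under Limitations and bias, the protocol article states the impact estimator: "We will perform the impact calculation through the double differentiation of the averages of the results found between the intervention and control clusters". The contrast is between the periods preceding and following the works. It adds: "The mitigation of bias will be carried out through the control of fixed effects of time and location". No term for the individual is mentioned there.

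The Statistical analysis section names models for two outcomes. Infection gets a quasi-Poisson rate ratio and a mixed-effects logistic model that allows for repeated measures on individuals. Soil load gets generalised linear models with random effects for study units. For well-being, the article says only: "The data will be collected preintervention and postintervention to evaluate the impact on well-being between arms".

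On follow-up, Study population and sample size says: "All participants from both intervention and control clusters will be followed over a period of 3 years after the sewerage intervention". The abstract describes five serological measurements, "one preintervention (baseline) and four postintervention". Two loss rates are given. Study population and sample size says: "We considered a potential loss to follow-up rate of 15%–20% per year". The sample size paragraph after the Figure 3 caption says: "Sample size estimates assumed a 12% annual drop-out rate across the 3-year study period". The stated response to loss is that "by including additional participants, we ensure the maintenance of an appropriate sample size for the outcomes that will be studied"; in context these are 420 people aged 6 months to 17 years.

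**The concern.** Each adult in this cohort has a pre-intervention value of his or her own. A difference of cluster averages does not use that link. As people leave, the set of adults inside a cluster changes between the before and after averages. A location fixed effect removes stable differences between clusters. It does not remove a change in who is observed within one.

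Allocation is not randomised, and only one arm receives sewerage works and the engagement that goes with them. Loss that depends on, say, income or health and differs between arms is therefore plausible, though the article does not document it. Such loss would add directly to the estimated effect on well-being and economic outcomes. Extra recruitment protects precision, not against selective loss.

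**Working it through.** **1. Cumulative loss.** With annual loss d, loss by the end of year 3 is 1 − (1 − d)³.
- d = 0.12: 1 − 0.681 = 31.9%, so 954 of 1400 remain.
- d = 0.15: 1 − 0.614 = 38.6%, so 860 remain.
- d = 0.20: 1 − 0.512 = 48.8%, so 717 remain.

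The article gives no cumulative figure to compare with these. If results are pooled over four equally spaced post-intervention surveys (assumed timing), the mean share missing is 21% at 12% per year and 33% at 20% per year.

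**2. Bias when nothing truly changes.** Put the outcome in SD units, with the same mean and variance at both times and within-person correlation r. Let Δ be the mean baseline value of stayers minus that of everyone enrolled in the arm. If leaving depends only on baseline, stayers' mean after the works is r × Δ. Then:
- Everyone seen at each time: r × (Δ_int − Δ_con).
- Same retained adults at both times: (r − 1) × (Δ_int − Δ_con), through regression to the mean.
- After-mean conditioned on each person's own baseline: rΔ − rΔ = 0.

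The first two results differ in size only through r against 1 − r, so no value of r brings both to zero. If Δ_int = Δ_con, all three are zero.

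**3. Numbers.** Assumed: r = 0.6, and a logistic probability of leaving with a stated slope per 1 SD of baseline. Its intercept is set to give the overall loss, and Δ is found by numerical integration.

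| Loss | Slope (intervention / control) | Δ_int − Δ_con | Everyone seen (× 0.6) | Retained only (× −0.4) |
|---|---|---|---|---|
| 32% | −0.25 / 0 | 0.079 | +0.05 | −0.03 |
| 32% | −0.5 / 0 | 0.152 | +0.09 | −0.06 |
| 32% | −0.5 / +0.5 | 0.303 | +0.18 | −0.12 |
| 49% | −0.25 / 0 | 0.120 | +0.07 | −0.05 |
| 49% | −0.5 / 0 | 0.230 | +0.14 | −0.09 |
| 49% | −0.5 / +0.5 | 0.461 | +0.28 | −0.18 |
| either | −0.5 / −0.5 | 0 | 0.00 | 0.00 |

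At the averaged loss of 21%, the everyone-seen bias for the three unequal patterns is 0.03, 0.06 and 0.12 SD. The signs reverse if the selection runs the other way.

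**4. Simulation check.** Four clusters per arm, 175 adults each, no true effect, 1500 trials per scenario. The simulated means agree with the table to within 0.002 SD. The version conditioned on own baseline is within 0.002 SD of zero throughout. The sampling SD of the everyone-seen contrast is about 0.06 at 32% loss and 0.07 at 49%, so the two stronger patterns exceed one sampling SD. Conditioning on baseline reduces that SD by 6–11%. These SDs include no between-cluster variation in change, which would raise them and shrink the relative gain.

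**5. When the remedy's assumption fails.** If leaving in one arm depends on the later value (slope −0.5, 32% loss), the bias is 0.15 SD for everyone seen, 0.10 SD for the baseline-conditioned version and 0.06 SD for retained adults.

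**The case against.** The estimator appears in two sentences under Limitations and bias, not in the Statistical analysis section, and those sentences name no outcome. Analysis sets and missing-data handling are usually left to a full protocol or SAP, neither of which is shown. This carries weight, and the absence of a missing-data section is not the point here. But an average-based double difference with time and location effects is a stated choice, and both natural readings of it are biased under differential selection.

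Several stronger readings are tempting, and the document does not support them:
- **That lost adults are counted before and not after.** The article never says who enters each average. Under the same selection, the two readings give opposite signs.
- **That any selective loss appears as an effect.** Equal selection in both arms cancels. Differential selection is assumed, and its strength is not known.
- **That 32–49% are missing from the after side.** That holds only at the end of year 3, because late leavers contribute to earlier surveys.
- **That the primary result is biased.** Infection has its own models. It is defined between consecutive surveys and there is only one baseline sample, so there is no pre-intervention incidence to difference.

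Scope has limits too. The abstract mentions transmission modelling for exposures, so contact and movement are less clear cases than SF-12, income and employment. Movement is measured on 40 residents per cluster, which affects precision but not the bias formula. Food insecurity and flood losses may be household measures, to which adult attrition does not map directly.

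Finally, the zero bias of the person-level version follows from simulating loss that depends only on baseline. Step 5 shows that it is not general protection.

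**Conclusion.** The point stands in a limited form. For outcomes measured on cohort members before and after, and not given a model under Statistical analysis, the stated double difference of averages is open to attrition bias that location and time effects do not remove. With 32% loss and the assumed selection patterns, the bias is about +0.05 to +0.18 SD if everyone seen is averaged and −0.03 to −0.12 SD if only retained adults are. At 49% loss, the ranges are about +0.07 to +0.28 SD and −0.05 to −0.18 SD. It is zero if loss is unrelated to the outcome or equally selective in both arms with a similar baseline mix. The loss rates come from the article; the correlation and selection slopes are assumptions. The better method is available at little cost, so the change should be made, but it concerns well-being and similar outcomes and not the trial's primary question.

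**What to change.** For outcomes measured on cohort members, replace the double difference of averages with a person-level one: a repeated-measures mixed model with a person random effect, cluster, survey time and an arm-by-period term. Keep the baseline values of people who later leave in the model. Person fixed effects would not do the same job: with two time points they reduce to the retained-adults comparison. Draw inference on the arm-by-period term at cluster or pair level, given four pairs. Keep cluster averages for outcomes not measured on people. State how this estimator relates to the models under Statistical analysis and to which outcomes it applies, and reconcile the 12% and 15–20% annual loss figures.

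The cost is wording only. Data collection and management already provides individual identifiers, and baseline values are collected. The downside is reliance on missing at random given observed values, so some bias remains if leaving depends on the unobserved later value. A sensitivity analysis for that case, with the retained-adults comparison alongside, would show how far the result depends on it. The gain in precision is small, roughly 5–12%, and is not the reason for the change.
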